### Nominated helpers

Participants can nominate one or more people to be an official helper. They may be family, friends or colleagues. They are not restricted to helpers from the UK. If individuals agree to be helpers, they will be directed to the study website where they will be able to access an information sheet about the study. They will be asked to signify their consent using an online form. This will indicate their consent to be a helper, for the study team to keep their contact details and also to signify whether they are willing to be contacted to complete an interview at a later date (for which there will be a separate consent process). They will then enter brief demographic details and their contact information on the website.

The ‘active’ phase of the intervention will run for 6 months where participants/helpers will receive reminders to use the system. After this period, they will still be able to access the intervention until 12 months but they will no longer receive reminders from the app.

### Exploring the feasibility of participants also acting as helpers

The HelpMeDoIt! study aims to explore how the intervention might work in a real-world setting. Due to the social support focus of the intervention, it may be that two or more friends/relatives wish to lose weight together and support each other. It is important to allow for and explore this for several reasons, including: (i) this approach may have potential benefits for participants via increased support and motivation; (ii) participants who also act as helpers might have more beneficial outcomes than participants who don’t act as helpers; and (iii) identifying a spillover effect in line with the diffusion of innovation theory (ie, the HelpMeDoIt! intervention gains momentum and spreads through a specific social network).^41^ Our study will therefore allow participants in the intervention arm to act as a helper for a friend/relative. Their helper will then also have access to the participant aspect of the intervention (ie, so that they can be both participants and helpers to each other). However, to avoid contamination of the findings the second individual will not be registered as a ‘study participant’ or randomised. If they were to be registered as a study participant, this could potentially contaminate the randomisation (ie, one individual may be randomised to the intervention group and the other to the control group). It is unknown if participants will choose to act as helpers but it is important to allow for and explore this as part of the feasibility study.

### The control group

The control group will receive a leaflet about the health benefits associated with healthy eating and physical activity behaviour change. They will not receive any social support or personalised content. Participants in the control group are not restricted in any way regarding their involvement in other weight loss activities. They can continue to embark on weight loss strategies, for example, join a slimming club. Controls can access the website and app after follow-up is complete at 12 months.

## Progression criteria from feasibility to full trial

The feasibility of the trial methods, the feasibility and acceptability of the intervention, and its potential to be further developed and delivered in a full randomised controlled trial are the key outcomes of this study. Feasibility will be assessed using the progression criteria outlined in table 2. These criteria have been finalised within our Trial Management Group and approved by our Trial Steering Committee. Final assessment of the progression criteria will be undertaken by the Trial Steering Committee following analysis of the findings. Multiple methods are employed to assess feasibility, including: (i) outcome measures; (ii) process evaluation measures; and (iii) an economic evaluation. There was substantial debate around criterion 6. On the one hand, current evidence on app usage indicates that around 25% of users will engage with an app only once.^42^ However, if only a minority of participants engage with the app and it is effective for them, then it may have a cost-effective and worthwhile impact on public health. On the other hand, we would want to see a reasonable proportion of participants engaging with the app sufficiently to set goals and identify helpers, even if the subsequent interactions with their helpers are not made via the app.

**Table 2 T2:** Progression criteria from feasibility trial to full randomised controlled trial

Progression criterion	Method of assessment
1. Is the intervention feasible to deliver and acceptable to participants and their helpers?	USE questionnaire Participant/helper interviews
2. Are participants willing to be randomised to the intervention?	Recruitment experiences of the study team and fieldworkers Insight from qualitative interviews with participants
3. Are appropriate and effective routes of recruitment available to achieve a powered sample size in a full trial?	Coming close to the sample size, as judged by the Trial Steering Committee (TSC), with reasonable expectations of being able to address any recruitment issues
4. Are identified barriers and challenges to implementation of the intervention planned for and surmountable?	Process evaluation which will present a SWOT analysis (Strengths, Weaknesses, Opportunities and Threats) and action plan
5. Are appropriate retention rates achieved at 12-month follow-up?	Measured using the following scale in both the intervention and control group at 12 months: if>70% followed up, proceed; if 50%–69% followed up, discuss with TSC; if<49% followed up, do not proceed
6. Do the majority (>50%) of participants within the intervention group visit the app at least twice or do 25% of participants randomised use it three or more times?	App usage statistics and/or participant interviews
7. Do the data collection procedures effectively collect the data required for a full trial? Successful completion of *at least one* data collection method (BMI, physical activity *or* healthy eating) at both baseline and at 12 months in those retained measured using the following scale:	If>90% *of at least one* data collection measure completed, proceed If 70%–89% *of at least one* data collection measure completed, discuss strategies for improvement in future trial with TSC If<70% *of all three* data collection measures completed, do not proceed without further modification and pilot
8. Are the intervention costs of a full trial covered?	Identification of a source to pay access and treatment costs

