#### Inclusion criteria

adults aged 18–70 years

BMI of ≥30 kg/m^2^
trying to lose weightaccess to a smartphone and the internet.

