#### Primary outcomes

Three primary outcomes will be assessed: BMI, physical activity and diet (table 3). Each will be measured at baseline and 12 months. We will assess which of these is most feasible for a future full trial. Since measuring diet^43^ and physical activity^44^ in community-based trials is challenging, we will assess two ways of measuring these outcomes. This will help inform the choice of primary outcome for a future full trial.

BMI (kg/m^2^) will be calculated from measures of height and weight. Height will be measured using a Seca Leicester Height Measuring Stadiometer, with participant facing forward, wearing no shoes and with their head in the Frankfort Plane (parallel to the floor). Measurements will be recorded once, in cm, to one decimal point. Weight will be measured, in the absence of shoes, using Tanita HD 352 High-Capacity Low-Profile Electronic Weighing Scales. Scales will be calibrated before first use. Weight will be recorded once, in kg, to one decimal point.

Physical activity will be measured using Actigraph GT3X accelerometers, objective activity monitors which measure duration, intensity and frequency of physical activity. Participants will be asked to wear the accelerometer on their right hip for 7 days during waking hours (except when swimming or bathing). Participants will receive their accelerometer during a face-to-face visit allowing correct placement of the device. This will be demonstrated by the researcher. Data will be collected in 1 s epochs, at a sample rate of 100 Hz, and converted to 15 s epochs for analysis using Actilife-6 software.^45^ Non-wear time will be identified by >60 min of continuous 0 counts and removed before analysis. Data will be included for analysis where the accelerometer has been worn for a minimum of 4 days, and with a minimum wear time of 10 hours per day. Freedson cut-points^46^ will be used to determine the amount of time spent sedentary and in moderate-to-vigorous physical activity.

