### Retention of participants

We will attempt to maintain good participant retention using several methods, including giving options for participants regarding where data collection takes place, provision of newsletter updates, sending birthday cards, obtaining mobile numbers and alternate contact details, offering a reduced item version of the follow-up questionnaire to provide at least a minimum data set for participants who are reluctant to complete the full follow-up and £20 voucher payments as a thank you for each point of data collection.

Participants have the right to withdraw consent for participation in the HelpMeDoIt! study at any time. If a participant initially consents but subsequently withdraws from the study, clear distinction will be made as to what aspect of the study the participant is withdrawing from. This could be: (i) withdrawal from the intervention; (ii) withdrawal from follow-up data collection; or (iii) withdrawal from entire study. Any retrospective request for data to be deleted will be respected.

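### Progression criterion 7 gives one pooled verdict that BMI alone can meet, so it cannot show which outcome or instrument is feasible, and its bands leave a gap just below the top threshold

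*Protocol article*

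**What the plan says.** Table 2, in the section on progression criteria, poses criterion 7 as "Do the data collection procedures effectively collect the data required for a full trial". What is scored is whether any one of three measures is complete ("BMI, physical activity *or* healthy eating) at both baseline and at 12 months in those retained"). There are three bands:

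- The top band is worded "If>90% *of at least one* data collection measure completed, proceed".
- The middle band covers 70% to 89%, again on any one measure, and sends the matter to the Trial Steering Committee to consider how a later trial could do better.
- The stop band is worded "If<70% *of all three* data collection measures completed, do not proceed without further modification and pilot".

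The Primary outcomes section names BMI, physical activity and diet as three primary outcomes and says of them "We will assess which of these is most feasible for a future full trial". It describes diet and activity as challenging to measure in community trials and sets up two methods for each: accelerometer and 7-day recall questionnaire for activity, DINE questionnaire and repeat 24-hour recall for diet. The stated purpose is to compare their feasibility and inform the choice of primary outcome. Criterion 7 does not say which method counts as the activity or the diet measure.

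BMI is also an inclusion criterion ("BMI of ≥30 kg/m^2") and a minimisation factor, and allocation follows baseline data collection. Under Retention of participants, follow-up may be shortened by "offering a reduced item version of the follow-up questionnaire to provide at least a minimum data set". What that minimum contains is not stated.

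**The concern.** The progression criteria are the key outcome of this study, and the Trial Steering Committee has to apply them as written. Criterion 7 collapses three outcomes and five instruments into one answer, set by whichever does best. BMI is the least demanding: one height and one weight reading at a visit. The accelerometer needs at least four days of ten hours' wear, and dietary recall needs four telephone contacts within ten days. A good BMI result can therefore carry the criterion while the harder measures fail, and the formal verdict would not record that they failed. The question the study set itself about activity and diet methods would then have no prespecified threshold behind it.

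The bands have a separate drafting fault. The top one starts above 90% and the middle one ends at 89%, so a result close to the decision boundary may have no verdict. The top two bands both say *at least one*, and no order of reading is stated.

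**Working it through.** **Inputs.** From Sample size: 120 recruited, 80 to intervention and 40 to control, 30% dropout expected. From Table 2: the three bands. Completion rates among those retained are not in the article, so they are assumed over a range.

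**The plan's own figures.** Retained: 120 × (1 − 0.30) = 84, of whom 80 × 0.70 = 56 are in the intervention arm. Half-width for a proportion: 1.96 × √(0.25/84) = 0.107, the stated ±11 points. Half-width for a mean: 1.96/√56 = 0.262 SD, as stated. These reproduce and are not in dispute.

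**What BMI alone can do.** With 84 retained, *proceed* needs at least 76 completers, since 75/84 = 89.3% and 76/84 = 90.5%. Take BMI 80/84 = 95.2%, activity 50/84 = 59.5% and diet 50/84 = 59.5%. One measure exceeds 90%, so the rule returns *proceed*. The stop band requires all three below 70% (58/84 = 69.0% or fewer), so it cannot be reached while BMI is at 59/84 = 70.2% or more, whatever happens to the other two.

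**How likely that is.** Let X be the number of retained participants with BMI at both time points, X ~ Binomial(84, p). The chance that BMI alone gives *proceed* is P(X ≥ 76). The chance of landing on the unassigned count is P(X = 75).

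| Assumed BMI completion p | P(X ≥ 76) | P(X = 75) |
|---|---|---|
| 85% | 0.10 | 0.072 |
| 90% | 0.53 | 0.136 |
| 92% | 0.77 | 0.095 |
| 95% | 0.975 | 0.015 |
| 97% | 0.999 | 0.0007 |

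**The gap.** Values above 89% and up to and including 90% meet neither of the top two bands. At n=84 and without rounding, that is exactly one count, 75/84 = 89.3%. If percentages are rounded to whole numbers, 75/84 reads 89% and is in the middle band, while 76/84 = 90.5% reads 90% and falls in the gap instead. There is no gap at 70%.

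**Order of the bands.** If each measure is checked against each band, BMI at 95% with diet at 75% satisfies both *proceed* and *discuss*. If only the best measure is scored, or the bands are read top-down, the answer is *proceed* alone. Table 2 does not say which reading applies.

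**The case against.** The strongest reply is that *at least one* is deliberate. The Primary outcomes section offers three candidates and says the study will find the most feasible. If the full trial needs one workable primary outcome, a best-of-three go/no-go rule is coherent. That stands. A reader might infer that criterion 7 cannot answer its own question, or that *proceed* should require BMI plus an activity and a diet instrument. Both inferences assume that the full trial needs all three domains, and the article does not say so.

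A reader might also infer that BMI passes almost automatically. Baseline BMI is needed for minimisation, so the test largely reduces to a 12-month weight in people already retained, and high completion is plausible. But no rate is given, the shortened follow-up could leave some retained participants without a weight, and the table above shows near-certainty only from about 95%. What needs no assumption is that BMI alone *can* meet the criterion.

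The overlap of the top two bands disappears on an ordered best-of-three reading, which is the natural one, so only the unstated order remains. The gap is about one participant wide, and the Trial Steering Committee makes the final assessment.

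Restricting to those retained might be read as hiding the usable yield. It does not: criterion 5 sets retention thresholds in both arms, and the Quantitative analysis section reports 12-month follow-up with 95% confidence intervals.

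Finally, methods are compared elsewhere, through interviews on the acceptability of the outcome measures and through precision stated for the proportion providing outcome data. That is so, but none of it attaches a threshold to an instrument.

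**Conclusion.** The point holds in a limited form. As written, criterion 7 returns one pooled verdict that BMI alone can meet with activity and diet both below 70%. That verdict cannot separate the three outcomes or the five instruments, which the protocol says it wants to compare, and the criterion does not define which activity or diet method is scored. This follows from the wording of Table 2 and needs no assumption.

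Its practical weight does rest on one. The chance of BMI passing alone runs from 0.10 to 0.999 as assumed completion goes from 85% to 97%, for 84 retained with independent participants. The gap is a genuine drafting error, but small: one count at n=84, with probability 0.136 if true BMI completion is 90% and 0.015 if it is 95%, taking the unrounded reading and BMI as the measure scored. The rule for overall progression is not wrong in itself. What is missing is a verdict per instrument.

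**What to change.** Reword criterion 7 in three respects.

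1. Make the bands contiguous: at least 90%, at least 70% but below 90%, and below 70%. State that they use unrounded percentages and are read top-down. With 84 retained, *proceed* still needs 76, and 75 now falls in *discuss*.
2. Apply the bands separately to BMI, accelerometer, 7-day activity recall, DINE and 24-hour dietary recall. *Proceed* then applies only to the instruments that reach the top band, and the others go to *discuss* or to modification and re-pilot.
3. Keep the overall at-least-one go/no-go rule if the committee wishes, and say that it concerns having one workable primary outcome for the full trial.

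Optionally, show paired completion as a percentage of all randomised beside the percentage of those retained. For example, 90% completion at 70% retention is 0.90 × 0.70 = 63% of those randomised.

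No new data are needed. The cost is one extra table and re-approval of the wording by the Trial Steering Committee, and some instruments may return *discuss* where the pooled rule would have said *proceed*.

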### Outcome measures

A full list of measurable outcomes is presented in table 3. Measures will be completed face to face with a study researcher, with the exception of one telephone-based outcome measure, in the participant’s home or an interview room in the university. All staff involved in data collection will be given training in study procedures, attend Good Clinical Practice training and hold a National Health Service (NHS) Research Passport from NHS Greater Glasgow and Clyde.

**Table 3 T3:** Outcome measures

Demographics		
Case report form: gender, age, socioeconomic status, employment and education status, current weight loss status, current health status, current computer and phone use		Baseline and 12 months
*Primary outcomes*		
Body mass index (kg/m^2^)	Physical measurement of height (m) and weight (kg)	Baseline and 12 months
Diet	DINE questionnaire^39^ 4 days of 24 hours dietary recall^40^	Baseline and 12 months
Physical activity	7-Day accelerometry^36^ 7-Day Physical Activity Recall Questionnaire^37^	Baseline and 12 months
*Secondary outcomes*		
Anthropometric changes	Waist and hip circumference (cm)	Baseline and 12 months
Health-related quality of life	EQ-5D questionnaire^41^ ICECAP-A scale^42^	Baseline and 12 months
Mental health	General Health Questionnaire^43^	Baseline and 12 months
National Health Service resource use and participant-borne costs	Specially designed resource use questionnaire	Baseline and 12 months
Usability of software	USE questionnaire^29^	12 months
Smoking use	Heaviness of Smoking Index^44^	12 months
Alcohol use	Alcohol Use Disorders Identification Test^45^	12 months
*Mediators of change*		
Social support	Exercise & Eating Habits Social Support Scales^46^	Baseline and 12 months
Self-efficacy	Weight^47^& Exercise Efficacy Lifestyle Scales^48 49^	Baseline and 12 months
Motivation	Treatment Self-Regulation Questionnaire^50^	Baseline and 12 months
Social networks	Sociogram^51^ Egocentric questionnaire^51^	Baseline and 12 months

#### Primary outcomes

Three primary outcomes will be assessed: BMI, physical activity and diet (table 3). Each will be measured at baseline and 12 months. We will assess which of these is most feasible for a future full trial. Since measuring diet^43^ and physical activity^44^ in community-based trials is challenging, we will assess two ways of measuring these outcomes. This will help inform the choice of primary outcome for a future full trial.

BMI (kg/m^2^) will be calculated from measures of height and weight. Height will be measured using a Seca Leicester Height Measuring Stadiometer, with participant facing forward, wearing no shoes and with their head in the Frankfort Plane (parallel to the floor). Measurements will be recorded once, in cm, to one decimal point. Weight will be measured, in the absence of shoes, using Tanita HD 352 High-Capacity Low-Profile Electronic Weighing Scales. Scales will be calibrated before first use. Weight will be recorded once, in kg, to one decimal point.

Physical activity will be measured using Actigraph GT3X accelerometers, objective activity monitors which measure duration, intensity and frequency of physical activity. Participants will be asked to wear the accelerometer on their right hip for 7 days during waking hours (except when swimming or bathing). Participants will receive their accelerometer during a face-to-face visit allowing correct placement of the device. This will be demonstrated by the researcher. Data will be collected in 1 s epochs, at a sample rate of 100 Hz, and converted to 15 s epochs for analysis using Actilife-6 software.^45^ Non-wear time will be identified by >60 min of continuous 0 counts and removed before analysis. Data will be included for analysis where the accelerometer has been worn for a minimum of 4 days, and with a minimum wear time of 10 hours per day. Freedson cut-points^46^ will be used to determine the amount of time spent sedentary and in moderate-to-vigorous physical activity.

The 7-day Physical Activity Recall questionnaire^47^ will be used to subjectively measure physical activity. Participants, guided by the researcher, will self-report their activity over the previous 7 days in relation to moderate, hard and very hard exercise. This measure has been validated for use in adult populations,^48^ and researchers will adhere to the protocol published by Sallis *et al*.^47^ Two methods of physical activity measurement are being explored to assess their feasibility and usability for a future trial.

Diet will be measured by the Dietary Instrument for Nutrition Education (DINE) questionnaire,^49^ a validated 7-item questionnaire to explore the frequency of consumption of different food types, for example, bread and rolls, cereals and meats. Fieldworkers will ask participants to report the frequency with which they eat specific foods. The frequencies will be scored using DINE guidelines^49^ to produce an overall score for fat and fibre. Diet will also be measured via repeat 24 hours dietary recall,^50^collected by a researcher via telephone on four separate days within a 10-day period (including one weekend day). Participants self-report their food intake, prompted by the researcher, for the previous 24 hours. Researchers will be guided by photographic and textual examples of portion sizes, which they can use as prompts over the phone. Participants food intake will be inputted onto dietary analysis software^51^ and analysed for energy intake, macronutrients and fibre. Two methods of assessing diet are being explored in order to assess their feasibility for a future trial.

